## Background

The Australian Institute of Health and Welfare has reported a national traumatic brain injury (TBI) incidence of approximately 107 per 100,000 population per annum [1]. Productivity loss, economic costs and ongoing disability associated with TBI render this health condition a significant global public health concern [1–3]. Traumatic brain injury is frequently followed firstly by a period of coma and secondly by a period of post-traumatic amnesia (PTA). In moderate to severe TBI, PTA represents a period of recovery spanning days to months wherein the patient experiences generalised cognitive disturbance. This cognitive state is characterised by anterograde and retrograde amnesia, confusion, disorientation, attentional dysfunction, low arousal and poor awareness [4–7]. Patients in PTA often exhibit severe neurobehavioural symptoms [8–10]. Perhaps the most challenging of these is agitation, defined as an excess of behaviour involving restlessness, disinhibition and emotional lability [11–13]. When using a standardised measure of agitation, approximately one third of individuals exhibit agitation during the early stages of recovery from TBI [11, 14]. Agitation is problematic for patients, families and healthcare workers. Restlessness may lead to falls, and aggressive behaviour may result in self-harm, destruction of property and violence towards others [15, 16]. Agitation is associated with poorer rehabilitation engagement and longer hospital stays, and agitated patients reportedly exhibit poorer functional outcomes and less frequent return to private homes [8, 14, 17, 18].

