### Participant timeline

The participant timeline is displayed in Table 1 schedule of activities.

**Table 1 Tab1:** Schedule of activities

Study phase	Screening/consent	Baseline/randomisation	Treatment period (PTA)	Post-PTA	Discharge	Three-month follow-up
ACD/ MTDM identification	X					
Trial introduction	X					
MTDM consent	X					
Screening	X					
Participant consent				X		
Randomisation		X				
Demographics^a^		X		X		
Medical record^b^		X	X		X	
Medical information^c^		X	X	X		
Blood test(s)^d^		X	X	X		
WPTAS		X	X			
ABS		X	X	X	X	
Simpson-Angus Scale		X	X			
Administer treatment			X			
Treatment log			X			
AE monitoring^e^			X			
RAVLT				X		
SDMT				X		
SF-12				X	X	X
FIM				X	X	
MPAI-4						X
PDHSUQ						X

^a^Age, gender, years of education, marital status, pre-injury employment/study status, drug and alcohol history, psychiatric history

^b^One or more of date and cause of injury, Glasgow Coma Scale, PTA duration, imaging results, surgical intervention, other injuries, Injury Severity Score, therapy hours and number of sessions, special nursing care, medication details, number of patients on ward

^c^Weight, BP, HR, WC

^d^Assessing fasting lipids, fasting glucose, HBA1C, creatinine

^e^Respiratory issues, lethargy, nausea, vomiting, difficulty swallowing, constipation, urinary retention, dizziness, seizures

#### Baseline—day 0

Following eligibility confirmation and randomisation, the following information will be gathered from the participant’s medical record: baseline WPTAS and ABS, demographic information (age, gender, years of education, marital status, pre-injury employment/study status, drug and alcohol history and psychiatric history) and medical information (date and cause of injury, Glasgow Coma Scale score, PTA duration, imaging results, surgical intervention, other injuries, injury severity score, therapy hours, special nursing care and medication details). Pre-treatment measures of weight, blood pressure (BP), heart rate (HR) and waist circumference (WC) will be conducted by nursing staff. Blood tests assessing fasting lipids, fasting glucose, haemoglobin A1c (HBA1C) and creatinine will be conducted. The Simpson-Angus Scale (SAS; [49]) will be completed by the patient’s treating physiotherapist, in order to assess the presence of extrapyramidal symptoms.

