#### Treatment—day 0 until emergence from PTA (or 6 months maximum)

The treatment period will last from day of completion of baseline assessments until the patient is deemed to have emerged from PTA or until 6 months have elapsed. Emergence from PTA is defined as the first of three consecutive days on which a score of 12/12 on the WPTAS is achieved. Participants will be administered their randomised dose. They will also receive optimal environmental management as per guidelines [7]. WPTAS and ABS scores will be recorded by nursing staff or the patient’s clinical neuropsychologist. Need for dosage escalation and rescue medication use will be monitored by study staff. To describe concomitant care and inform health-economic evaluation, the number of patients on the ward, therapy hours and number of sessions and medication use including name and dose regimen will be recorded from the participant’s medical file.

AE monitoring will occur weekly. Clinically significant changes in these parameters will be recorded as AEs and a decision made by the treating doctor in consultation with a psychiatrist and the DSMC as to whether serious AEs necessitate withdrawal from the study.

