#### Secondary outcomes

To examine the safety of olanzapine administration in PTA patients: Difference between olanzapine and placebo groups’ mean number of AEs (as captured via trial bloodwork, Adverse Events Questionnaire, Simpson-Angus Scale, measures of weight, BP, HR, WC) during PTA.To determine whether olanzapine treatment reduces the number of clinically agitated days during PTA: Difference between olanzapine and placebo groups’ mean number of clinically agitated days (ABS score > 21) during PTA.To determine whether olanzapine treatment alters level of agitation at hospital discharge: Difference between olanzapine and placebo groups’ mean ABS score at discharge, controlling for ABS score at treatment commencement.To determine whether olanzapine treatment alters level of cognition in PTA: Difference between olanzapine and placebo groups’ mean levels of PTA as measured using the WPTAS [44, 45], controlling for WPTAS score at baseline. Mean scores will encompass daily assessments of the WPTAS throughout the treatment period, from first day of treatment until emergence from PTA (defined as the first of three consecutive days on which a score of 12 on the WPTAS is obtained). The WPTAS is commonly used in Australia to assess PTA. Seven items on the WPTAS assess orientation to time, person and place, and five assess anterograde memory (therapist face, name and three picture cards). Good construct validity and inter-rater reliability have been demonstrated [45, 61]. Nurses and clinical neuropsychologists who administer the WPTAS at Epworth HealthCare are trained in its use.To determine whether olanzapine treatment alters PTA duration: Difference between olanzapine and placebo groups’ mean number of days in PTA (from date of injury until emergence from PTA based on three consecutive scores of 12 on the WPTAS).To determine whether olanzapine treatment alters cognitive performance following PTA emergence:

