4. Adverse Events Questionnaire—This questionnaire will prompt reporting of AEs expected due to olanzapine use. This questionnaire will be completed weekly throughout the treatment period by the participant’s treating physician in partnership with study staff. Symptoms assessed will include respiratory issues, lethargy, nausea, vomiting, difficulty swallowing, constipation, urinary retention, dizziness and seizures. Information to be collected includes event description, start date, severity, relatedness to treatment, action with investigational product, expectedness, seriousness, outcome, end date and classification.

Clinically significant changes in these parameters will be recorded as AEs. Adverse events will be tabulated and tracked in a password-protected electronic file. All AEs will be followed to adequate resolution or stabilisation, including those that persist beyond the treatment period. If AEs continue beyond hospital discharge, follow-up will occur via telephone.

The DSMC will be informed of all serious AEs. A decision will be made by the treating doctor in consultation with a study psychiatrist and the DSMC as to whether withdrawal from the study, dose reduction or rechallenge is necessary.

Notification and reporting of AEs will be carried out according to the Australian regulatory, ethics committee and International Conference on Harmonisation Good Clinical Practice guidelines.

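### The safety outcome does not solicit falls, self-harm or injury to others, so whether these harms of agitation are counted depends on unprompted recording

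*Protocol article*

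**What the plan says.** All references are to the Protocol article.

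- **Secondary outcomes, first item.** Safety is the between-group difference in the mean AE count over the PTA period, with AEs "as captured via trial bloodwork, Adverse Events Questionnaire, Simpson-Angus Scale, measures of weight, BP, HR, WC". The parenthesis names the capture sources and adds no residual category.
- **Harms, item 4.** On the Adverse Events Questionnaire: "This questionnaire will prompt reporting of AEs expected due to olanzapine use". Its content follows: "Symptoms assessed will include respiratory issues, lethargy, nausea, vomiting, difficulty swallowing, constipation, urinary retention, dizziness and seizures". The treating physician completes it weekly with study staff.
- **Participant timeline, Table 1, note e.** The AE-monitoring row is glossed with the same nine symptoms as a plain list: "Respiratory issues, lethargy, nausea, vomiting, difficulty swallowing, constipation, urinary retention, dizziness, seizures".
- **Harms, after item 4.** The recording rule is "Clinically significant changes in these parameters will be recorded as AEs". The treatment-period section repeats it: "Clinically significant changes in these parameters will be recorded as AEs and a decision made by the treating doctor".
- **Background.** The harms of agitation are given as: "Restlessness may lead to falls, and aggressive behaviour may result in self-harm, destruction of property and violence towards others".
- **Statistical methods.** AE counts, together with other safety measures that are not defined there, are to be analysed by Poisson or negative binomial regression.

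**The concern.** The first secondary aim is the safety of olanzapine in patients in post-traumatic amnesia (PTA). The trial is justified by the harm that agitation does, and the Background says what that harm is. If the drug works, falls and injuries might become fewer. If it makes patients drowsy or dizzy (lethargy and dizziness are both on the questionnaire as expected effects), falls might become more frequent. Either result would bear directly on the safety question.

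The plan asks every week about nine expected drug effects. It schedules vital signs, weight, waist circumference, bloods and the Simpson-Angus Scale, and it nowhere asks about falls or injuries. Capture is therefore unequal by type of harm: systematic for expected side effects, and dependent on someone volunteering the event for the harms that treatment is meant to prevent. A difference between arms in the resulting AE count could be read as the safety answer although one side of the balance was not collected in a comparable way.

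**Working it through.** **1. Which sources feed the safety count, and does any of them solicit a fall, self-harm or injury to others?**

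| Source named in the outcome | What it solicits | Falls, self-harm, injury to others? |
|---|---|---|
| Bloodwork | Fasting lipids, fasting glucose, HBA1C, creatinine | No |
| Weight, BP, HR, WC | Physical measurements | No |
| Simpson-Angus Scale | Extrapyramidal signs | No |
| Adverse Events Questionnaire | Nine named symptoms | Not named |

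The questionnaire is the only source through which such an event could enter.

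**2. Can the questionnaire hold an unprompted event?** Yes. Its symptom list in Harms is introduced with an open verb. The information to be recorded includes an event description, expectedness, seriousness and classification, and an expectedness field would have little use if only expected events could be entered. Against this, Table 1 note e gives the nine symptoms as a plain list, and the recording rule in both places refers back to the listed parameters. On the text, an unprompted fall may be recorded, but nothing makes its recording systematic.

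**3. Does another outcome count these events?** None of the secondary outcomes counts falls or self-harm. Two parts of the plan touch aggression:

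- The ABS, the primary outcome, rates 14 agitated behaviours. It does not record injuries that follow from them.
- Rescue olanzapine may be given for physical aggression that threatens staff or property, and the Discussion says rescue doses will be compared between groups. That is an indirect and discretionary marker of aggression. It carries no information on falls or self-harm.

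**4. What could 58 participants show?** The group size comes from the primary outcome in Sample size: standardised difference 0.80, power 0.80, two-sided alpha 0.05. The two-sample t test gives n = 25.52, so 26 per group, as stated. With 10% attrition, 26/(1 − 0.10) = 28.9, so 29 per group and 58 in total, also as stated.

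The protocol gives no rate of falls or injuries. For illustration only, take assumed proportions p1 and p2 of participants with at least one fall, with n = 29 per arm and p̄ = (p1 + p2)/2:

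power = Φ{ [ |p1 − p2| − 1.96·√(2p̄(1 − p̄)/n) ] / √( [p1(1 − p1) + p2(1 − p2)]/n ) }

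For 30% versus 15%, p̄ = 0.225. The null standard error is √(0.34875/29) = 0.1097 and the alternative standard error is √(0.3375/29) = 0.1079. Power is then Φ[(0.15 − 0.2149)/0.1079] = Φ(−0.60) = 0.27.

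| Assumed proportions | Power, 29 per arm |
|---|---|
| 20% vs 10% | 0.18 |
| 30% vs 15% | 0.27 |
| 40% vs 20% | 0.38 |
| 30% vs 10% | 0.48 |

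Even a halving of the proportion would usually be missed, so these events call for descriptive reporting by arm and not for a further test.

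**The case against.** The strongest reply is that nothing in the text excludes these events. The recording rule says that changes in the listed parameters are AEs; it does not say that nothing else is. The list in Harms is introduced as ways of monitoring, not as a definition. The questionnaire is open-ended, is completed by a physician, and is itself one of the counted sources, so a fall entered there would count. Serious AEs go to the data safety monitoring committee, and reporting follows Good Clinical Practice. Aggression reaches the comparison through the ABS and rescue doses. Finally, this is a condensed article, and the full protocol (version 1.4) may carry a general AE definition and the form itself.

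Much of this stands. A reader might infer that only the listed parameters can be AEs, or that falls, self-harm and assaults never enter the comparison. The open wording and the event fields do not support that, and aggression is partly reflected elsewhere.

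The rest does not remove the point. The reporting clauses govern notification; they do not turn an unsolicited event into a systematically collected one, and a non-serious fall need not reach the committee. The other safety measures in Statistical methods are undefined. As for condensation, the article itself states the outcome, its sources, the prompted items and the recording rule, and the point rests on those statements. If the full protocol already solicits these events, the article's wording should be brought into line with it.

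**Conclusion.** The point holds in a limited form. As written, the plan solicits expected olanzapine effects every week and leaves falls, self-harm and injury to others to unprompted recording, with no outcome defined for them. The safety comparison is therefore uneven in what it collects. It is not shown to be blind to these events.

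No size can be put on the loss. Multiplying 58 by an assumed event rate would give the number of participants who have such an event, not the number whose event goes uncounted; the second figure also needs the premise that none is recorded, which the text does not support. Nor do the documents show that these are the commonest harms, or that the listed symptoms would arise mainly under olanzapine. That the drug could move falls or injuries either way is a plausible inference from the protocol's own account of agitation and of expected effects, not a documented finding.

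This is a worthwhile amendment to safety data collection. It affects neither the primary outcome nor the sample size.

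**What to change.** 1. In Secondary outcomes (first item), the treatment-period section and Harms, state that any untoward event from first dose is an AE, whether volunteered, observed or found in the record, and that the questionnaire is a prompt and not a boundary. Bring Table 1 note e into line.
2. Add three items to the weekly form: falls, self-injury, and injury to staff or other patients. Take them from the medical chart, which study staff already review to check treatment administration.
3. Report these events by arm as a separate descriptive line (participants with at least one event, and number of events) beside the count of expected olanzapine effects, without a further hypothesis test.

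**Cost.** A few items on a form already completed weekly and one extra line in a table, with no new visit or procedure. The total AE count becomes larger and more mixed, which the separate line handles. Trial status reports 5 participants recruited, so a change at that stage would give prospective capture for nearly all of the planned 58.

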### Inclusion criteria

(1) Currently under hospital care at Epworth HealthCare for TBI rehabilitation, (2) a history of blunt head trauma with a loss of consciousness and an initial Glasgow Coma Scale of 3–14 and/or a period of PTA, (3) judged to be in PTA (score < 12) on the Westmead Post Traumatic Amnesia Scale (WPTAS; [44, 45]), (4) judged to be in a state of clinically significant agitation (score > 21) on the Agitated Behaviour Scale, (5) aged 18 years or older, (6) provision of signed and dated Medical Treatment Decision Maker Participant Information and Consent Form by the participant’s Medical Treatment Decision Maker (MTDM; during PTA) and (7) provision of signed and dated Participant Information and Continuing Consent Form by the participant (upon PTA emergence).

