### Recruitment

Patients admitted to the Epworth HealthCare ABI Unit are routinely screened for PTA status using the WPTAS on admission. Those deemed to be in PTA have the WPTAS and ABS completed on a daily basis by a clinical neuropsychologist or nurse until they emerge from PTA. Study staff will be alerted to potential participants by ABI ward staff. Potential participants include patients in PTA who are exhibiting clinically significant agitation or thought likely to become agitated (due to factors such as agitation during acute hospitalisation). Due to their confusion and inability to lay down new memories, patients in PTA are not cognitively capable of consent. Recruitment will therefore target the patient’s MTDM. This will follow a two-stage process. Firstly, the study will be introduced to the patient’s MTDM by a member of their treating medical team and verbal consent for contact from study staff will be gained. Rapid consent processes are important to recruitment given the time-limited nature of PTA. The decision to introduce the trial to MTDMs of those patients determined likely to become agitated (rather than only those presently agitated) has been made in an effort to expedite the recruitment process and avoid exclusion of eligible participants. Agitation levels of those patients not presently agitated are monitored by study staff. If consent for contact is obtained and the patient is agitated at any stage during PTA, study staff will then contact the MTDM to carry out study consent procedures.

Participant recruitment commenced in June 2019, with the aim of recruiting participants until June 2022. Given that the full study protocol will have a duration of approximately 3 months, on average, data collection will continue until the end of September 2022. Epworth HealthCare treats more than 110 new patients with TBI annually, of whom 80 are likely to be in PTA on admission. Recent research studying this population within the Epworth HealthCare ABI ward [26] showed that 42.4% of TBI patients exhibited significant agitation according to the ABS whilst in PTA. Therefore, approximately 34 patients in PTA are likely to exhibit clinically significant agitation annually. Allowing for declined consent and ineligibility, we envisage recruitment of our sample over a 41-month period.

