Difference between olanzapine and placebo groups’ mean total words recalled over five trials on the RAVLT [50]. The RAVLT is a 15-word cognitive list learning task. This test is sensitive to memory impairments in TBI populations [62] and has good psychometric properties [63].Difference between olanzapine and placebo groups’ mean number of items completed on the SDMT [51]. The SDMT is a test of processing speed, requiring transcription of numbers corresponding with symbols from a key over 90 s. Use of the oral version of this test will avoid effects of motor weakness on performance. The oral SDMT has excellent psychometric properties [64].Difference between olanzapine and placebo groups’ mean number of errors on the SDMT.

Epworth HealthCare clinical neuropsychologists who will administer these measures are trained and experienced in their use.
7.To determine whether olanzapine treatment alters length of inpatient hospital stay: Difference between olanzapine and placebo groups’ mean length of inpatient hospital stay, measured in days from day of admission until day of discharge from inpatient care.8.To determine whether olanzapine treatment alters functional independence at discharge and 3-month follow-up:

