### Statistical methods

#### Analysis of primary and secondary endpoints

Descriptive statistics will be reported using frequencies and percentages for categorical data. Percentages will be calculated based upon the number of patients for whom data are available. Continuous or dimensional variables will be summarised using means and standard deviations, with medians and interquartile ranges (difference between 25th and 75th percentiles) reported for potentially skewed data such as SF-12 PCS and MCS scores.

For the analysis of the primary endpoint, difference in mean daily ABS scores during PTA between olanzapine and control groups, a mixed model/multilevel regression framework [72], taking into account duration of PTA, will be employed. Although a difference between group means corresponding to a large effect size (0.80 of the pooled group standard deviation) is expected, a clinically significant improvement is defined as a difference in group means of the mean daily ABS scores within PTA equal to at least half a pooled group standard deviation difference, the minimal clinically important difference for improvement in irritable/aggression scale scores in TBI [68]. In regard to secondary endpoints, regression methods appropriate to the type of outcome variable will be employed. Comparison of the two groups on dimensional secondary endpoints such as ABS at discharge and WPTAS scores will be analysed using linear regression or median quantile regression. Median quantile regression, based upon the median and so less affected by very high or very low scores, will be employed for possibly skewed variables, such as SF-12v2 MCS and PCS scores, that may not meet the assumptions of linear regression [73].

Secondary endpoints involving count data including number of days in PTA, number of clinically agitated days, length of stay in hospital, agitation scores on discharge, number of “treatment failures” and number of AEs and other measures of treatment safety will be analysed using regression models for count data (Poisson or negative binomial regression as appropriate; [74]).

All statistical tests will be two-tailed, with alpha or statistical significance level set to *p* < 0.05. 95% confidence intervals will be reported throughout. The number of missing observations will be reported. Analyses will assume intention to treat, with all patients analysed as randomised.

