#### Cost-effectiveness analysis

In line with the main analysis, the primary outcome for the economic evaluation will be mean score on the ABS during PTA. Secondary outcomes for the economic evaluation will be FIM at hospital discharge and quality-adjusted life years to 3-month follow-up calculated using SF12-based Six-Dimensional Health State Short Form (SF6D) scores derived using recently published Australian weights [70]. Treatment effects with respect to the ABS and FIM will be estimated as for the main analysis. Treatment effects with respect to the SF6D index score and total quality-adjusted life years to 3-month follow-up will be estimated using one-part generalised linear models, controlling for SF6D index scores at pre-treatment and specifying appropriate variance and link functions [77].

Patient-level data on total cost during inpatient rehabilitation admission will be extracted from patient medical records to capture medication use, therapy hours, length of stay and special nursing care. Post-discharge health service utilisation will be estimated from patient/MTDM self-report (at 3-month follow-up) regarding use of primary care, prescription and over-the-counter medications, allied health care, community care and paid and unpaid home-help as reflected on the PDHSUQ. Productivity gains/losses will be estimated based on length of inpatient hospitalisation, FIM scores at discharge and MPAI-4 scores at 3-month follow-up. Given the likely structure of our data and the advice of Buntin and Zaslavsky [78], treatment effects with respect to total cost will be estimated using one-part generalised linear models with gamma variance function and a log link (rather than transformed ordinary least squares or two-part models), controlling for patient characteristics at pre-treatment.

Results will be expressed as (i) cost per point improvement on the ABS, (ii) cost per point improvement on the FIM, and (iii) cost per quality-adjusted life year gained. We will summarise sampling error and parameter uncertainty using the bootstrap acceptability method to calculate confidence intervals and generate cost-effectiveness acceptability curves [77].

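### PTA duration is counted from injury and length of stay from admission, so both comparisons include pre-randomisation days that dilute the ratio and usually cost precision

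*Protocol article*

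**What the plan says.** In the protocol article, Secondary outcomes, item 5 is the difference between arms in "mean number of days in PTA (from date of injury until emergence from PTA based on three consecutive scores of 12" on the WPTAS. Item 7 is the difference in mean length of inpatient stay, "measured in days from day of admission until day of discharge from inpatient care". The section on analysis of primary and secondary endpoints treats both as counts: "Secondary endpoints involving count data including number of days in PTA, number of clinically agitated days, length of stay in hospital" and several further outcomes go to Poisson or negative binomial regression.

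Exposure starts later than either clock. The first inclusion criterion is "Currently under hospital care at Epworth HealthCare for TBI rehabilitation", so injury and admission are already past at entry. Under Recruitment, "Agitation levels of those patients not presently agitated are monitored by study staff", and consent follows once contact has been agreed and "the patient is agitated at any stage during PTA, study staff will then contact the MTDM to carry out study consent procedures". Screening, possible weaning from existing agitation medication, and randomisation come next. Only then does exposure begin: "The treatment period will last from day of completion of baseline assessments until the patient is deemed to have emerged from PTA".

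Item 4, the WPTAS level during PTA, is handled differently. Its window opens on the first day of treatment, and it is adjusted for the baseline score. Items 5 and 7 state neither feature.

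**The concern.** Each participant brings a block of days, of varying length, that was settled before allocation. It adds the same expected amount to both arms and spread to every individual value. It carries no information about the drug.

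The Background and the Abstract's discussion both raise the possibility that olanzapine prolongs PTA and hospital stay, and secondary aims 5 and 7 are there to find out. The trial has 58 patients and was sized for the ABS. If a real prolongation is shown as a ratio nearer to 1, with a wider interval, the likely reading is that no harm was seen.

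**Working it through.** **1. The plan's own figure.** Inputs from the Sample size section: standardised difference 0.80, two-sided alpha 0.05, power 0.80. The two-sample t-test solution is 25.52, rounded up to 26 per group. With 10% attrition, 26/(1 − 0.10) = 28.9, rounded up to 29. Both figures reproduce, but they concern the ABS. The documents give no effect size or SD for PTA days or stay, and no distribution of days from injury or admission to randomisation. Those inputs are assumptions below, shown over a range.

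**2. Difference in means.** Write total days as T = A + B, where A is the days before randomisation and B the days after. Randomisation balances A in expectation, so the expected difference in T equals the expected difference in B. There is no bias. The variance is Var(A) + Var(B) + 2Cov(A, B).

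**3. Ratio of means.** Let s be the share of the control mean that precedes randomisation, and RR the true ratio for B. The ratio for T is s + (1 − s)RR.

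| s | RR = 1.5 | RR = 2.0 |
|---|---|---|
| 25% | 0.25 + 0.75 × 1.5 = 1.375 | 1.75 |
| 50% | 0.50 + 0.50 × 1.5 = 1.25 | 1.50 |
| 75% | 0.75 + 0.25 × 1.5 = 1.125 | 1.25 |

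**4. Precision on the mean scale.** Let k = SD(A)/SD(B) and ρ be the correlation of A and B. The standardised difference on T is d/√(1 + k² + 2ρk). Take d = 0.8 on B purely as a reference, with 26 per group; power on B is then 0.807. Power on T:

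| k | ρ = −0.25 | ρ = 0 | ρ = 0.3 |
|---|---|---|---|
| 0.25 | 0.832 | 0.784 | 0.729 |
| 0.5 | 0.807 | 0.716 | 0.623 |
| 1.0 | 0.637 | 0.516 | 0.419 |

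At ρ = 0, restoring 80% power would need 28, 32 or 51 per group. The loss vanishes when k² + 2ρk ≤ 0, that is when ρ ≤ −k/2.

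**5. The model named in the plan.** Negative binomial regression was simulated with 26 per group and 600 replicates per row. Days were log-normal, with a control mean of 20 days after randomisation, CV 0.6 and a true ratio of 1.6. The correlation applies on the log scale. Monte Carlo error is at most about √(0.25/600) = 0.02.

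| Mean pre-days (CV) | Correlation | Ratio on total | Power, days from randomisation | Power, total | Power, total adjusted for log pre-days |
|---|---|---|---|---|---|
| 10 (0.5) | 0 | 1.40 | 0.87 | 0.83 | 0.86 |
| 10 (0.5) | 0.4 | 1.41 | 0.86 | 0.77 | 0.91 |
| 20 (0.5) | 0 | 1.30 | 0.86 | 0.71 | 0.84 |
| 20 (0.5) | 0.4 | 1.31 | 0.87 | 0.64 | 0.91 |
| 30 (0.5) | 0 | 1.24 | 0.87 | 0.60 | 0.83 |
| 30 (0.5) | 0.4 | 1.23 | 0.86 | 0.43 | 0.90 |
| 20 (0.8) | 0 | 1.31 | 0.87 | 0.57 | 0.85 |
| 20 (0.8) | 0.4 | 1.30 | 0.83 | 0.49 | 0.90 |

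The ratios agree with step 3: (10 + 32)/30 = 1.40, (20 + 32)/40 = 1.30 and (30 + 32)/50 = 1.24. With adjustment the ratio is still only 1.24 to 1.41, so the covariate returns power but leaves the ratio diluted.

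**The case against.** The strongest reply is that the outcomes are defined as differences in mean days, which randomisation protects. A ratio of total days is also a correct ratio of the quantity the protocol chose. That stands. A reader might infer that the trial's estimate is biased towards no harm, but the documents do not support this. What is lost is sensitivity, and the ratio answers a question about total time instead of the time treatment could affect.

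A reader might also hold that entry conditional on still being in PTA (left truncation) invalidates the count model. The entry rule acts before allocation and equally in both arms. In a separate simulation with gamma-distributed days (26 per arm, 400 to 500 replicates per cell), type I error was 4–8% under either definition.

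The size of the loss is assumed, and no power is claimed for these outcomes. That stands too. The figures in step 5 picture PTA duration and should not be carried over to stay. Admission cannot precede injury, and discharge usually follows emergence, so the pre-randomisation share of stay is generally smaller. The early approach to decision makers described under Recruitment also shortens that interval.

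Covariates are commonly left to the analysis plan, which is not shown and may include time to randomisation. If so, most of the power complaint is answered. The time origin is different: the protocol fixes it in the outcome definition, and a covariate does not undo the dilution.

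Two extensions are tempting and should not be made. The count of clinically agitated days during PTA is not shown to start before treatment: the Primary outcome section equates ABS during PTA with the treatment period, and Table 1 labels the column likewise. For cost, the plan says "Patient-level data on total cost during inpatient rehabilitation admission will be extracted from patient medical records", which does span earlier days. However, the incremental result is an adjusted difference in mean cost, modelled with control for pre-treatment characteristics, and a balanced earlier cost does not dilute a difference.

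**Conclusion.** The point holds for items 5 and 7. That both clocks start before randomisation is stated in the text, and the dilution of a ratio of means follows by arithmetic once s is above zero. It assumes that the count models report a ratio through the conventional log link, which the protocol does not spell out.

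The loss of precision is usual but not certain, and its size is open. On the mean scale, power of 0.807 falls to between 0.784 and 0.516 as k goes from 0.25 to 1.0 with uncorrelated parts. It falls further with positive correlation and not at all once ρ reaches −k/2.

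The primary endpoint and the sample size are untouched. The change is still worth making, because these two outcomes are meant to reveal prolongation and the weakness favours a reassuring result.

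**What to change.** For the treatment comparison, define item 5 as days from randomisation to the first of three consecutive days at 12/12 on the WPTAS, and item 7 as days from randomisation to discharge. Keep PTA duration from injury and stay from admission as descriptive figures by arm.

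If the injury and admission origins are kept for the comparison, prespecify log days from injury (item 5) or from admission (item 7) to randomisation as a covariate, adding one day before taking logs if zeros can occur. State that the resulting ratio refers to total days.

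The cost is a change of wording in two outcome definitions. The injury date is already collected, and the admission, randomisation and discharge dates are hospital or trial records, so no new data are needed. The one drawback is less direct comparability with PTA duration counted from injury, and reporting both meets it.
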